### SAFER pregnancy study: data analysis plan

The proportion of women who quit smoking or alcohol use at the primary endpoint will be calculated as the number of women that have quit at this endpoint divided by the total number of women included in the study. Furthermore, we will use (backward) logistic regression analysis to explore independent predictors of effectiveness of the intervention. Descriptive statistics will be used for the secondary outcomes and results will be reported in narrative and tabular form. Open questions within the questionnaires will be evaluated qualitatively using thematic content analysis.

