### SAFER pregnancy study: sample size calculation

Because vulnerable populations, as our target population, are difficult to reach and recruit for participation in medical research^57,58^ and because we aim to develop an intervention fit for the target population, we decided at this stage to pragmatically perform an uncontrolled before−after study. The overall aim is to obtain an estimate of potential effectiveness of the SAFER pregnancy intervention, while assessing its feasibility and acceptability. As such, findings from this study are ideally placed to inform design of a potential larger randomised experiment. The primary outcome is the proportion of women attaining sustained cessation of alcohol use and/or smoking. Because little research on interventions for alcohol cessation during pregnancy exists and only a small number of women were referred to the focus group study due to alcohol consumption, we based our sample size calculation primarily on smoking cessation. In a recent randomised controlled trial assessing the effectiveness of incentives to promote smoking cessation during pregnancy, 22.5% of the women in the intervention group reached the primary endpoint of cessation, versus 8.6% in the control group^59^. Accordingly, we set our true proportion to 25% and our null hypothesis proportion to 9%. With a power of 90% and a one-sided alpha of 2.5%, our intervention group would have to contain 49 participants in order to assess effectiveness of the SAFER pregnancy intervention versus the counterfactual scenario. Considering an expected dropout of 25%, we aim to include 66 women, who smoke and/or consume alcohol, at baseline.

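### The dropout allowance assumes that about 49 of 66 women are analysed, but the primary proportion is taken over all 66; if the 25% quit rate is a completer rate, power is about 72%, not 90%

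*Protocol article*

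**What the plan says.** The section on the sample size calculation sets a null proportion of 9% and a true proportion of 25%. It takes these from a randomised trial of incentives in which "22.5% of the women in the intervention group reached the primary endpoint of cessation, versus 8.6% in the control group". It continues: "With a power of 90% and a one-sided alpha of 2.5%, our intervention group would have to contain 49 participants". The dropout step follows: "Considering an expected dropout of 25%, we aim to include 66 women".

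The data analysis plan says that the proportion quitting at the primary endpoint is "calculated as the number of women that have quit at this endpoint divided by the total number of women included in the study". It makes no exception for women who drop out. The outcomes section requires cessation to be biochemically validated at the endpoint. The data collection section specifies CO and urinary cotinine tests for smoking at that point, and a PEth test for alcohol.

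**The concern.** Dividing 49 by 0.75 makes sense if 17 or so of the 66 women vanish from the analysis and about 49 remain, of whom 25% quit. Under the stated estimator they do not vanish. A woman who drops out and gives no validated sample stays in the denominator and cannot enter the numerator. Dropout then lowers the expected proportion; it does not reduce the number analysed.

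The 90% is the only statement in the article of how well the study can tell the intervention's quit rate from the 9% benchmark. If it rests on a different analysis set from the one planned, readers may put too much weight on a result that fails to clear 9%. The same mismatch could also pass into the sizing of the larger randomised study that this one is meant to inform.

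**Working it through.** **Inputs.** From the sample size section: p0 = 0.09, p1 = 0.25, one-sided alpha 0.025 (z = 1.960), power 0.90 (z = 1.2816), dropout 25%. From the data analysis plan: the denominator is all women included, here 66.

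**1. Reproduce the plan's figures.** One-sample normal approximation, with the null variance under p0 and the alternative variance under p1:

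n = [(1.960 x sqrt(0.09 x 0.91) + 1.2816 x sqrt(0.25 x 0.75)) / (0.25 - 0.09)]^2 = [(0.5609 + 0.5549) / 0.16]^2 = 48.6, so 49.

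Dropout: 49 / 0.75 = 65.3, so 66.

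Both stated figures are reproduced.

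**2. Expected proportion under the planned denominator.** Assume that 25% of completers quit and that no dropout supplies a validated quit:

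0.75 x 0.25 + 0.25 x 0 = 0.1875.

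**3. Power with 66 women by the same normal formula.** Power = Phi[((p - 0.09) x sqrt(66) - 1.960 x sqrt(0.09 x 0.91)) / sqrt(p(1 - p))].

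- p = 0.1875: (0.0975 x 8.124 - 0.5609) / 0.3903 = 0.592, power 72.3%.
- p = 0.25: (0.16 x 8.124 - 0.5609) / 0.4330 = 1.706, power 95.6%.

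**4. Power with 66 women by an exact binomial test.** The smallest cut-off that keeps one-sided alpha within 2.5% is 12 or more quitters, with actual alpha 1.4%.

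- p = 0.1875: power 59.7%.
- p = 0.25: power 92.7%.

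| Meaning of the 25% | Expected proportion of 66 | Normal formula | Exact test |
|---|---|---|---|
| Rate among completers | 18.75% | 72% | 60% |
| Rate among all included | 25% | 96% | 93% |

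**5. Between the two readings.** If the proportion among all included were 20%, power would be 79.7% (normal) or 69.1% (exact). At 22.5% it would be 90.0% or 83.8%.

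**6. Scale of the gap.** On the completer reading, 90% power with an all-included denominator would need about 119 women by the normal formula (118.4 rounded up).

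**The case against.** The strongest reply is that the 25% need not be a completer rate. The source rate of 22.5% is worded as a share of the women in the intervention arm, which reads as all participants. If the 25% carries the same meaning, dropout is already inside it, and 66 women give 93% to 96% power. This stands. A reader might infer that the 90% is simply not delivered, and the article does not support that flat statement. The reply does not reconcile the text, however, because on this reading there was no reason to inflate 49 to 66 for dropout.

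A reader might also infer that 49 is itself wrong, because an exact test on 49 women (10 or more quitters, alpha 1.1%) has only 82% power. The article does not support this either. The 49 is a correct normal-approximation result and no test is named. The uncorrected z-test that matches the formula (9 or more of 49) has power 89.5%, though its actual alpha is 2.9%. Nor is 49 the planned denominator.

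It is also fair to say that the drop from 72% to 60% comes from moving to an exact rule. The 72% is the figure on the plan's own method and should be read first.

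Finally, the study is presented as feasibility work that yields an estimate of potential effectiveness, and no go/no-go decision is tied to rejecting 9%. That limits the harm. It does not remove the conflict, since the article still claims 90% power to assess effectiveness.

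**Conclusion.** The sample size and the primary analysis assume different analysis sets, and the article does not reconcile them. No stated number is miscalculated; the fault is that the dropout allowance does not match the denominator. On either reading one stated element has to change:

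- If 25% is a completer rate, which the allowance implies, the 90% becomes about 72% by the plan's formula (about 60% exact).
- If 25% is a rate among all included women, which the wording of the source rate suggests, the allowance is redundant and power is about 96% (about 93% exact).

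These figures assume that exactly 66 women are included, that dropout is 25%, and that no dropout provides a validated quit. If some did, the completer-reading figures would be higher.

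Because both the denominator and the inflated sample size are fixed in the article, this is a conflict between stated items and not a detail left to a fuller document.

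**What to change.** Keep the all-included denominator and reword the two sections:

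- State that women lost before the endpoint count as not having quit.
- State whether the 25% and the 9% describe all included women or completers.
- Restate the power for 66 women to match. If 25% is a completer rate, this is about 72% (normal) or 60% (exact). If it is an all-included rate, remove the dropout adjustment and give about 96% (normal) or 93% (exact).
- Give the power for the test that will actually be used against 9%. If that test is exact, recompute the cut-off for the number of women enrolled, since 12 or more holds for 66.

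The cost is a few sentences, and possibly a less favourable stated power. No extra women are needed: a study meant to produce an estimate and assess feasibility can keep its target of 66 as long as the power is stated correctly.

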### SAFER pregnancy study: study design

The SAFER pregnancy study is a prospective, uncontrolled before−after study.

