### SAFER pregnancy study: data collection

Participants receive questionnaires through e-mail and fill them out online. They receive a voucher worth 15 euros if they filled out the questionnaire.

Questionnaire items are listed in Table 4. Participants receive a questionnaire at inclusion and 1 week before each group session. Women who are pregnant during the study period also receive a questionnaire at 34−38 weeks gestation and a final questionnaire 1 week postpartum. Women who do not become pregnant during the study period receive their final questionnaire after the sixth group session. In addition, a log on patient recruitment, collaboration with local entrepreneurs, and contact with healthcare providers and participants will be kept by the research team to explore barriers and facilitators for implementation of the intervention. In the log quantitative data will be noted, such as the number of potential participants referred and included and the amount of incentives provided (outcome measures are shown in Table 3). In addition, participants will fill out questionnaires about their experiences with the intervention and study itself during their participation and at the end of their participation. These data will give insight into acceptability and feasibility of the SAFER pregnancy intervention and therefore potential barriers and facilitators for proper implementation can be identified. These potential barriers and facilitators will be further qualitatively evaluated in a focus group study at the end of the SAFER pregnancy study, with the aim to evaluate the acceptability and feasibility of the intervention, in three separate focus groups with participants, leaders of the group sessions and involved healthcare providers.

**Table 4 Tab4:** Data collection with questionnaires.

Data group	Data item
Baseline characteristics	Age
	Parity
	Ethnicity
	Household income and financial problems
	Educational level
	Marital status and relational problems
	Due date
	Lifestyle behaviour (smoking, alcohol use, diet, activity, drugs)
	Statements concerning lifestyle changes according to the Attitude—Social influence—Self-efficacy (ASE)-model
	Statements concerning identity
Level of addiction	Age started smoking
	Number of cigarettes smoked per day
	Smoking partner
	Intention and motivation to quit
Obstetric characteristics	Use of birth control
	Number of living children
	Number of miscarriages/stillbirths
	Number of premature births

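### Backward logistic regression on about 12 to 16 quitters in a single arm can show only factors associated with cessation, unstably selected, and not predictors of the intervention's effectiveness

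*Protocol article*

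**What the plan says.** The section on the data analysis plan first defines the primary proportion (women who quit, divided by all women included) and then adds: "we will use (backward) logistic regression analysis to explore independent predictors of effectiveness of the intervention". This fixes both the selection method and the target of inference. The article does not give a candidate list or a retention threshold.

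The study design section reads: "The SAFER pregnancy study is a prospective, uncontrolled before−after study". The Discussion names the missing control group as a limitation of the study, without applying it to this regression.

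The sample size section supplies the numbers that set the event count: "we set our true proportion to 25% and our null hypothesis proportion to 9" (per cent); "With a power of 90% and a one-sided alpha of 2.5" (per cent); "our intervention group would have to contain 49 participants"; "Considering an expected dropout of 25%, we aim to include 66 women".

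The only listing of collected covariates is Table 4 in the data collection section. It has about 22 items, some of which are blocks of several statements, for example the entry that begins "Statements concerning lifestyle changes according to the Attitude". The article does not say that these items are the candidates for the regression.

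**The concern.** There are two separate problems.

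The first is the target. A predictor of effectiveness is a factor that changes the difference between quitting with and without the intervention. Every woman here receives the intervention, so that difference is never observed at any level of any covariate. A factor associated with quitting may simply mark women who would have quit anyway.

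The second is the method. Backward elimination starts from the model that contains every candidate and discards terms according to the data. With few events the starting model is poorly determined, small changes in the data change which terms survive, and the surviving odds ratios tend to be too far from 1. The p-values and intervals of the final model are computed as if no selection had taken place.

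At stake is a results table that presents chance associations, or ordinary prognostic factors, as independent predictors of how well the intervention works.

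**Working it through.** **Reproducing the plan's sample size.** Inputs from the sample size section: null proportion 0.09, true proportion 0.25, one-sided alpha 0.025, power 0.90, dropout 25%.

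n = [1.960·√(0.09·0.91) + 1.282·√(0.25·0.75)]² / (0.25 − 0.09)² = 48.6, rounded up to 49. Then 49 / 0.75 = 65.3, rounded up to 66. Both stated figures reproduce.

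**Expected quitters.**
- 25% of the 49 evaluable women: 12.25.
- 25% of all 66 women: 16.5.
- 66 women with dropouts counted as not having quit: 0.25 × 0.75 = 18.75%, and 0.1875 × 66 = 12.4.

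**Events per candidate** (12.25 and 16.5 divided by the number of candidates).

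| Candidates | Events per candidate |
|---|---|
| 5 | 2.5 to 3.3 |
| 10 | 1.2 to 1.7 |
| 20 | 0.6 to 0.8 |
| 22 (all Table 4 items, an assumption) | 0.56 to 0.75 |

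**What one arm can identify.** On the plan's own assumptions, 9% would quit without the intervention and 25% with it. If nobody is kept from quitting by taking part, 0.09 / 0.25 = 36% of the quitters would have quit anyway: 49 × 0.09 = 4.4 of 12.25, or 66 × 0.09 = 5.9 of 16.5. The data do not show which quitters these are, so the model describes both kinds together.

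**False selection with noise only.** Backward elimination by Wald tests was simulated with independent noise candidates, n = 66 and 18.75% quitters (200 to 300 runs per setting). The last two columns give the chance of at least one false positive among K independent tests.

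| K | Any kept, p<0.05 | Any kept, p<0.10 | 1 − 0.95^K | 1 − 0.90^K |
|---|---|---|---|---|
| 8 | 30% | 53% | 34% | 57% |
| 12 | 41% | 73% | 46% | 72% |
| 16 | 53% | 85% | 56% | 81% |

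A second simulation used likelihood-ratio tests, a 25% quit rate and n = 49 and 66 (150 runs per setting). At p<0.05 it kept at least one noise variable in 43% to 46% of studies with 10 candidates, 63% to 66% with 15 and 73% to 83% with 20. Plain multiplicity would give 40%, 54% and 64%.

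**Share of noise when some predictors are real.** Here two or three true predictors were assumed, with odds ratios of 1.5 to 2.0 per standard deviation and retention at p<0.05 (120 runs per setting, n = 49 and 66). Noise made up 26% to 55% of the selected variables with 10 candidates, 42% to 77% with 15 and 62% to 85% with 20.

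**Failure of the full model.** With 16 candidates, n = 66 and 18.75% quitters, about 8% of fits failed. With 20 candidates the rate was about 7% to 10% at n = 66 and 25% quitters, 28% at n = 66 and 18.75%, and 54% to 58% at n = 49.

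**The case against.** The strongest reply is that the analysis is announced as exploratory, that the Discussion already concedes the missing control group, and that a logistic model of cessation can only be about cessation, so the reference to effectiveness is just loose wording. All of this limits the seriousness, and the primary proportion is untouched. It does not remove the problem. The article still names a target that the design cannot estimate, and a selection method that is unreliable at this event count under any label.

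A reader might also infer several stronger points that the documents do not support.

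- *That the candidate list is long.* Table 4 describes questionnaire content, and nothing ties it to the regression. The list may stand in a full analysis plan, so its absence from the article is not a fault.
- *That the selected variables will be mostly noise.* A noise-only simulation cannot show this, because everything it selects is noise by construction. With true predictors included, noise is clearly the majority at 20 candidates and usually at 15, but not at 10.
- *That the model will often fail to fit.* This needs about 15 to 20 or more candidates, together with the smaller sample or event count.
- *That backward elimination itself creates the 30% to 53% false-selection rate.* Those figures are close to what the same number of independent tests would give. The excess in the second simulation appears mainly at 15 and 20 candidates. Univariable results read as significance tests would produce false positives at a similar rate.
- *That the predictors are intended to steer the larger trial.* The Introduction, sample size section and Discussion say that the study's findings as a whole may inform it. They give the predictors no such role.

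**Conclusion.** The point holds in a limited form. That one arm cannot yield predictors of the intervention's effectiveness follows from the design alone and needs no assumption about candidates. That backward selection is unreliable here follows from the plan's own 12 to 16 expected quitters: even a short list of 5 candidates leaves only 2.5 to 3.3 events each.

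The simulated sizes rest on independent candidates, on retention thresholds of 0.05 or 0.10 that the article does not state, and, for the noise shares, on assumed effect sizes. Fewer than one event per candidate applies only if the list is about as long as Table 4.

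This is a defect in a secondary, exploratory analysis. It is worth correcting because the correction is cheap, but it does not affect the primary result.

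**What to change.** - Rename the target: factors associated with cessation. State that effect modification is left to a randomised trial.
- Replace backward selection with two or three prespecified predictors that apply to smokers and drinkers alike, for example pregnancy at inclusion and motivation to quit. Fit them in one Firth-penalised logistic model and keep all terms. Table 4 lists motivation beside smoking items, so confirm that it is also asked of women who only drink.
- Use smoking-specific predictors, such as cigarettes per day or a smoking partner, only among women who smoke. Eligibility also admits women who only drink, for whom cigarettes per day has no useful meaning.
- Show all other factors as descriptive univariable estimates with confidence intervals, and say that these are not to be read as tests.

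Three terms leave 12.25 / 3 = 4.1 to 16.5 / 3 = 5.5 events per term. That is still few, which is why the penalised fit and the exploratory label should both stay.

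The cost is a change of method in the analysis text and fewer factors in the adjusted model. It needs no new data, visits or participants.

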### SAFER pregnancy study: sample size calculation

Because vulnerable populations, as our target population, are difficult to reach and recruit for participation in medical research^57,58^ and because we aim to develop an intervention fit for the target population, we decided at this stage to pragmatically perform an uncontrolled before−after study. The overall aim is to obtain an estimate of potential effectiveness of the SAFER pregnancy intervention, while assessing its feasibility and acceptability. As such, findings from this study are ideally placed to inform design of a potential larger randomised experiment. The primary outcome is the proportion of women attaining sustained cessation of alcohol use and/or smoking. Because little research on interventions for alcohol cessation during pregnancy exists and only a small number of women were referred to the focus group study due to alcohol consumption, we based our sample size calculation primarily on smoking cessation. In a recent randomised controlled trial assessing the effectiveness of incentives to promote smoking cessation during pregnancy, 22.5% of the women in the intervention group reached the primary endpoint of cessation, versus 8.6% in the control group^59^. Accordingly, we set our true proportion to 25% and our null hypothesis proportion to 9%. With a power of 90% and a one-sided alpha of 2.5%, our intervention group would have to contain 49 participants in order to assess effectiveness of the SAFER pregnancy intervention versus the counterfactual scenario. Considering an expected dropout of 25%, we aim to include 66 women, who smoke and/or consume alcohol, at baseline.

### SAFER pregnancy study: ethics and dissemination

The Medical Research Ethics Committee of the Erasmus MC approved the study (NL67428.078.18). All participants will provide written informed consent. Each participant will receive a study number and all identifiable information of the participant and her baby will be stored separately from other data collected during the study. Only the core researchers ([name], [name] and [name]) will have access to the identification list and the access passwords for both datasets. Study documents and data will be stored for 15 years after completion of the study.

### SAFER pregnancy study: safety

Due to the negligible risks of the SAFER pregnancy study, we will not collect or report adverse events and a Data Safety Monitoring Board will not be established. In concordance with the Guideline for Good Clinical Practice, the study will be monitored at least once a year by an independent and qualified monitor.^60^

## Discussion

Design of the SAFER pregnancy study was based on literature, guidelines, and results of the focus group study described here alongside the final protocol of the SAFER pregnancy study.

A major strength of the SAFER pregnancy intervention, embedded in existing primary care networks, is that it has been developed in close collaboration with the target population. Strengths of the focus group study in itself were that we identified barriers and facilitators for cessation by including women who continued to smoke and women who quit smoking during pregnancy in two different groups. In doing so, every participant was able to speak freely without the risk of feeling judged. Although we did not collect objective information regarding socio-economic indicators from focus group participants, many of them shared information during the discussions indicative of having a low socio-economic status (e.g. poor financial status, unemployment, single status, former drug abuse). Due to this, we believe the participants of the focus group study were representative for the target population of the SAFER pregnancy study. Limitations of the focus group study were the low number of participants and the fact that alcohol use was low among included women. Another strength of the SAFER pregnancy intervention is that it combines several interventions previously shown to be effective in promoting cessation of smoking and/or alcohol use. Also, the intervention addresses different aspects of addiction (e.g. identity, stress) and besides providing preliminary data on potential effectiveness this study we will assess facilitators and barriers to implementation of the intervention. Together the findings of the study may thus inform the design of a larger randomised trial to assess the impact of the SAFER pregnancy intervention on cessation and birth outcomes. Limitations of our study are that we will not have a control group and that, due to a lack of financial resources, we are unable to actively engage partners in the intervention.

The innovative SAFER pregnancy approach can potentially bring about substantial health benefits for mothers and children by addressing two important and common risk factors for adverse pregnancy outcomes which are entirely preventable.

